### Phase 2: Enhanced Social Network Strategy (ESNS) Intervention

In adapting the CDC’s SNS, we retained the original intervention’s 4-step model while renaming the steps with revised terminology that is more person-forward [41] and better meets the needs of our key population (see Figure 5). We will make several adaptations to SNS. Before phase 1, we had planned for eSNS service linkage to include PrEP linkage or care re-engagement (not only HIV testing, unlike SNS) and to embed eSNS within a public health department’s partner services program. Following phase 1, we also widened our key population to include English and non–English-speaking groups disproportionately affected by HIV in North Carolina (although all ambassadors must be able to provide informed consent in English), and, guided by formative data and recommendations of CAG members, developed a process for referrals from community sites to engage key population members outside of partner services (described further in the Results section).

**Figure 5. F5:**
[figure not shown]
Schematic diagram of enhanced social network strategy (eSNS) procedures, displaying the 4-step intervention structure and revised terminology. SNS: social network strategy; DIS: disease intervention specialist; PrEP: pre-exposure prophylaxis.

#### Step 1: Finding Community Ambassadors

We will use 3 strategies to enroll a planned sample of at least 20 community ambassadors per year: (1) invite eligible priority network members identified during routine partner services, (2) publicize the study with local community organizations and clinics who provide HIV-related services to the study’s key population, and (3) invite eligible peers to become ambassadors.

For (1), DIS coaches will inform individuals contacted during partner services investigation of priority networks (recent HIV transmission networks involving our key population) about eSNS. To reach networks with the highest probability of recent HIV transmission [42], we will collaborate with NC DHHS to prioritize index persons diagnosed with acute incident HIV infection [43] for assignment to DIS coaches. Following completion of partner services activities, DIS coaches will invite interested clients who meet inclusion criteria to become ambassadors. Eligible clients include people recently diagnosed with HIV, named partners of people recently diagnosed with HIV, or genetic cluster members re-engaged with HIV care who were identified through cluster detection protocols. Ambassadors do not have to be living with HIV.

Based on recommendations from phase 1, for (2) we will identify potential ambassadors through community-based recruitment in addition to partner services. Through partnerships with local CBOs that offer HIV-related services to our key population, we will post print materials at clinic and community venues and distribute digital recruitment materials through social media platforms. For (3), previously referred peers may become ambassadors, facilitating deeper penetration into networks and recruitment of new peers who have not previously been reached. Eligible peers will be contacted by a DIS coach for a brief program orientation before providing informed consent to serve as ambassadors. Newly identified ambassadors will replenish ambassadors who completed peer outreach (Step 3).

#### Step 2: Ambassador Coaching

Following orientation and informed consent, DIS coaches will deliver a semistructured coaching session to ambassadors. Coaching is a core component of eSNS designed to foster rapport and to develop an individualized action plan for contacting peers. We adapted CDC’s SNS Coaching Guide [44] to accommodate findings from Phase 1 formative data and integrated our guide into Network Canvas (Complex Data Collective), an open-source software interface using intuitive visuals to collect personal network data [45]. DIS coaches are encouraged (but not required) to hold the first coaching session in person. All coaching sessions must take place in a private location. Ambassadors will receive a US $35 gift card for completing the coaching session.

During the first coaching session, ambassadors will be prompted to identify people in their social network (peers) whom they believe would benefit from linkage to HIV prevention or treatment services, including but not limited to sexual or injecting partners. Collectively, these peers comprise each ambassador’s outreach network. In addition to demographic information, ambassadors will be asked to provide each peer’s first name and last initial (or nickname or pseudonym). The DIS coach will guide the ambassador through a semistructured conversation to create a unique action plan to contact each peer (see Multimedia Appendix 1). DIS coaches will advise ambassadors that they do not need to disclose their HIV status or medical history and will help devise conversational strategies to manage situations where peers may ask about the ambassador’s HIV status. At the first coaching session, ambassadors will be supplied with printed and digital referral cards to distribute to peers in their outreach network (see Figure 6).

**Figure 6. F6:**
[figure not shown]
Example referral card that ambassadors distribute to peers during the enhanced social network strategy (eSNS) outreach period. Each ambassador has a unique ID and image (bottom right). The QR code and URL link to a contact form uniquely associated with each ambassador. Peers who complete the contact form have unique codes that link to the ambassador’s referral card.

#### Step 3: Peer Outreach

In step 3, ambassadors will approach each peer identified in their outreach network to give them a unique referral card (associated with the ambassador’s study identifier) and encourage them to contact the eSNS team for assisted linkage to HIV services (see Figure 6). There will be no predetermined limit on the number of referral cards ambassadors can disperse, although DIS coaches will be trained to guide ambassadors to select peers whom they believe will benefit from one or more HIV services (Step 4). Peers indicate their interest by submitting a contact form to request that the eSNS team reach out to them, calling the eSNS team directly, or meeting the DIS coach in person at a time and location facilitated by the ambassador (eg, for field-based HIV testing).

We anticipate that ambassadors will engage in peer outreach for approximately 2‐6 weeks, during which DIS coaches will contact ambassadors at least weekly for brief follow-up coaching to encourage them to complete their peer outreach plan or to discuss strategies to adapt it. During follow-up coaching, new peers may be identified by the ambassador. Peer outreach will conclude when an ambassador has saturated all potential peers in their outreach network or 6 weeks have elapsed since the first coaching session, whichever comes first. Our referral period of 2‐6 weeks is a practical application of ongoing coaching and booster sessions described in implementation guidance, as SNS is based on short-term coaching [44]. Grounds for dismissal earlier than the 6-week cut-off include coercing a peer’s participation, ambassadors and peers knowingly misrepresenting their identities to obtain gift cards, repeatedly referring people not part of their network or who are ineligible, or unreliable communication following enrollment.

#### Step 4: Linking Peers to HIV Services

After a peer initiates contact with the study team, the DIS coach will attempt to follow up with that peer within 24 hours for a study screening visit. The purpose of the screening visit is to explain the study’s aims and for the DIS coach to verify whether a peer is eligible for linkage to HIV services. DIS coaches will first ask peers for their ambassador’s name to validate against the code and image on that ambassador’s referral card. Ambassadors will be compensated with a US $20 gift card per peer in their outreach network who completes screening, even if they do not enroll in the study intervention. Ambassadors will only receive compensation for a maximum of 5 peers’ screening visits (US $100 total in gift cards), although more than 5 peers may be referred.

Peers will be offered assisted linkage to HIV prevention and care services available in the Charlotte region. First, informed consent and Health Insurance Portability and Accountability Act (HIPAA) authorization will be obtained from Peers to permit the eSNS team to obtain data regarding the outcomes of scheduled HIV service appointments at community-based sites. Before scheduling appointments, DIS coaches will assess peers’ preferences among local care and prevention service providers and whether they prefer to be accompanied by their ambassador. If peers prefer, DIS coaches may also meet peers at a private location for field-based HIV testing or accompany them to a testing site. For peers who do not present with clinical symptoms of acute HIV infection, DIS coaches may perform rapid HIV testing (OraQuick HIV or bioLytical INSTI HIV dual testing) according to North Carolina DHHS protocols. Peers who test positive or indeterminate following field-based rapid testing will receive counseling by DIS coaches and expedited linkage to HIV care and bridge counseling (see the Ethical Considerations section for more detail on DIS training). Peers who reside in South Carolina and cannot attend appointments in the Charlotte region will be linked to HIV services available in Columbia, South Carolina but will not be eligible to become ambassadors.

For HIV testing, peers will be offered testing if they have never previously tested or if their last HIV test occurred more than three months prior and yielded negative or unknown results. Peers living with HIV will be linked to initial care if they are newly diagnosed or never entered care; or re-engaged with care if previously diagnosed but not currently engaged in care. Care engagement is defined as both having had a clinic visit within 12 months and currently taking ART. Peers will be offered facilitated linkage to PrEP if HIV test results obtained within the prior three months were confirmed non-reactive and they have never been on PrEP, or if they previously took PrEP but have not received a PrEP prescription in the past 6 months.

Peers will receive US $20 gift cards for attending each of up to 2 HIV service appointments, US $40 total in gift cards (eg, completing both HIV testing and attending a PrEP initiation appointment). The study team will obtain and document all HIV test results. For peers choosing to engage in HIV services at a community site unaccompanied by a DIS coach, the eSNS team will contact the site and provide the HIPAA authorization to confirm that the peer attended the appointment and, as applicable, to obtain their HIV test results. Peers may also choose to self-disclose their attendance or results to the eSNS team with a photo or screenshot. Following linkage, peers may be invited to enroll as community ambassadors and initiate the intervention cycle again by participating in coaching (Step 2) and peer outreach (Step 3).

### Ethical Considerations

The study was approved by the University of North Carolina at Chapel Hill Institutional Review Board (IRB #22‐1988). Intervention procedures were determined to present minimal risks to participants, which include potential loss of confidentiality or emotional distress caused by the potentially sensitive nature of discussing HIV or receiving an HIV diagnosis following testing facilitated by the study. Ambassadors and enrolled peer participants will provide informed consent. All DIS credentialed in North Carolina, including DIS coaches, are trained to address psychological consequences resulting from an HIV or STI diagnosis, which includes specific modules on linking people to services (medical, behavior, and social support), in-person training, and ongoing mentorship with senior DIS. The eSNS team will follow applicable North Carolina DHHS and IRB procedures for lawful reporting of safety concerns, logging unanticipated events involving study participants, and referrals to social services agencies.

Research that leverages peer relationships can create ethical dilemmas around how to minimize the risk of coercion among peers and protect the confidentiality of participants who may know each other [46]. Creating a peer outreach plan will require asking for information about individuals who are not yet enrolled—and may never enroll—in the study intervention. To avoid a scenario where identifiable information is indirectly collected about unconsented peers (making them “secondary subjects”), only first names and last initials or pseudonyms will be recorded during coaching. Despite this precaution, peers contacted by ambassadors may have unpredictable reactions to receiving outreach or discussing HIV services, including assuming that sensitive or identifiable information was provided about them. However, as no personal identifiers will be recorded unless peers initiate screening, the study team will have no way of contacting (or identifying) peers until peers contact the study team. Once peers engage in screening, DIS coaches will explain that no data collected by the study team will be shared with the ambassador who referred them.

Compensation for peer outreach was structured to minimize the possibility of creating a financial incentive for ambassadors to coerce peers into research participation. Ambassador gift cards for peer referrals are limited in both number (maximum 5) and amount (US $20). Providing ambassadors gift cards for one of their peers completing a screening visit, rather than for enrolling in the study or completing an HIV service appointment, ensures that ambassadors are fairly compensated for time spent recruiting peers while avoiding a scenario where their compensation is contingent on peers’ enrollment or participation in the study’s intervention. The screening visit includes a description of the study and eligibility survey performed by a DIS coach, who will be trained to emphasize to peers that participation is voluntary, and peers who choose not to participate but who still wish to receive HIV services (eg, HIV testing) will be provided a referral to a community site.

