### Data Sources and Management

The REDCap platform hosted at UNC Chapel Hill is a HIPAA-compliant web-based platform that will serve as a central repository for data collected by the study team, including administration of ambassador and peer e-consent forms, participant recruitment and enrollment tracking, and collection of screening, appointment results, and survey data. Public health surveillance data obtained from the North Carolina Electronic Disease Surveillance System (under a data sharing agreement with North Carolina DHHS) will be stored in a secure cloud drive and REDCap. We plan to routinely analyze HIV sequences reported to the state and associated case-level epidemiological data to facilitate timely response to clusters within NC DHHS’s Region II (Charlotte).

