From interviews with members of our key population who self-identified as Black or African American, we found that privacy and flexibility in HIV prevention and care services were important themes. We have adopted recommendations to allow appointment scheduling for peers at nontraditional times, having DIS coaches offer peers discreet, field-based HIV rapid testing, ensuring time in between appointments to avoid peers crossing paths, and allowing ambassadors to choose their preferred mode of coaching (in-person or phone call). Finally, confusion arose about intervention roles (DIS coaches vs ambassadors) during qualitative data collection with both HIV services providers and key population members. We will train DIS coaches to clearly communicate the structure of the compensation process, and that peers may choose whether to be accompanied by their ambassador to service appointments, and that under no circumstances will ambassadors be able to access their peers’ protected health information or study data.

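### Peers are promised that no study data reach the ambassador, yet the ambassador is paid for each peer who completes screening and can infer who was screened

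*Protocol article*

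**What the plan says.** Two places promise confidentiality towards the ambassador without qualification. Ethical Considerations states that "DIS coaches will explain that no data collected by the study team will be shared with the ambassador who referred them". The Results section, describing what coaches will be trained to communicate, adds that "under no circumstances will ambassadors be able to access their peers’ protected health information or study data".

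Three other places bear on whether that promise can be kept:

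- Data Sources and Management describes REDCap as the repository for, among other things, "collection of screening, appointment results, and survey data".
- Step 4 sets the referral payment: "Ambassadors will be compensated with a US $20 gift card per peer in their outreach network who completes screening". It is due whether or not the peer goes on to enroll.
- Step 4 also caps it: "Ambassadors will only receive compensation for a maximum of 5" peers' screening visits, US $100 in all, although more peers may be referred.

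Ethical Considerations explains why payment hangs on screening, "rather than for enrolling in the study or completing an HIV service appointment": to avoid a financial motive for coercing peers. It does not discuss what the payment tells the person who receives it.

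**The concern.** Completion of screening is a fact recorded by the study team. Paying on that fact passes it to the ambassador, at least as a count. The ambassador named the peers during coaching and approached them personally, so a count can often be turned into a name.

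Loss of confidentiality is one of the risks the article names, and privacy was an important theme in its formative interviews. A peer who completes screening and then declines to enroll still triggers a card. That peer's attendance may become known after a coach has said that nothing would be shared. A missing card can be informative too: it may show that a peer did not attend, which invites the pressure on peers that the payment structure was meant to limit.

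**Working it through.** **Step 1. Scope of the promise.** Ethical Considerations covers all data the study team collects. The Results section covers health information and, separately, study data. Neither makes an exception for attendance at screening.

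**Step 2. Is completed screening within that scope?** Yes. Data Sources and Management lists screening among the data collected by the study team.

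**Step 3. The payment rule.** US $20 per screened peer, at most 5 peers: 5 × 20 = US $100, which reproduces the total stated in Step 4.

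**Step 4. What a payment conveys.** Let an ambassador approach *m* peers and receive *k* cards.

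- In every case up to the cap, the ambassador learns that *k* of the *m* were screened.
- If *k* = *m*, every peer is known to have been screened. If *k* = 0 when outreach closes, none was.
- If 0 < *k* < *m* and payment is not itemised by peer, only the count is revealed.
- If cards are issued as screenings occur, a card that arrives while only one peer is outstanding identifies that peer.
- Beyond five screened peers, payment reveals nothing more.

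The article does not say when cards are issued or whether they are itemised, so the share of peers identified under the plan cannot be computed.

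**Step 5. What a payment does not convey.** It follows screening regardless of enrollment or service use, so it carries no HIV status, test, result, PrEP history or enrollment.

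**Step 6. Illustration for the least revealing schedule.** Suppose a single un-itemised sum is paid at the close of outreach. Assume each peer screens independently with probability *p*; the documents give no such figure. For networks up to the cap, everyone's attendance is known when all or none screened:

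P(all known) = *p*^m + (1 − *p*)^m

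| Peers approached (m) | p = 0.5 | p = 0.3 or 0.7 |
|---|---|---|
| 1 | 0.5 + 0.5 = 1.00 | 0.3 + 0.7 = 1.00 |
| 2 | 0.25 + 0.25 = 0.50 | 0.09 + 0.49 = 0.58 |
| 3 | 0.125 + 0.125 = 0.25 | 0.027 + 0.343 = 0.37 |
| 5 | 0.031 + 0.031 = 0.06 | 0.002 + 0.168 = 0.17 |

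These figures include networks in which nobody screened and no card was paid. The chance that a payment positively identifies every peer as screened is *p*^m alone. For five peers that is 0.002 at *p* = 0.3, 0.031 at *p* = 0.5 and 0.168 at *p* = 0.7.

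Sample Size and Power Estimates assumes 5.0 peers per ambassador but expects most ambassadors to have few, so the upper rows of the table matter.

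**The case against.** The best defence is in the Results section. The sentence that carries the absolute promise also says coaches will be trained to explain how compensation is structured. If peers hear that explanation, they can work out what a card reveals. This stands in part: it softens the problem. But the article does not say that peers are the audience for it, and the unqualified promise remains beside it.

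Second, payment logistics may properly be left to the full protocol. This also stands: silence on timing and itemisation is not a fault, and it would be wrong to claim that every payment identifies a peer. The conflict between the promise and the payment trigger, though, lies between two things the article does state.

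Third, the payment was deliberately separated from enrollment and service use. This is correct, and it limits the harm to attendance at screening.

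A reader might infer two further leaks that the documents do not support:

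- One route for a peer to show interest is "meeting the DIS coach in person at a time and location facilitated by the ambassador (eg, for field-based HIV testing"). It is one of three routes. What the ambassador learns there comes from taking part rather than from data the team hands over, and being accompanied to service appointments is the peer's choice.
- Ambassadors may be dismissed for "repeatedly referring people not part of their network or who are ineligible". This could be read as exposing a peer's HIV, testing or PrEP history. Read with Textbox 1 and Overview of Key Roles, ineligibility here most naturally means age, network membership or location. Nothing says the ambassador learns which peer was ineligible or why. The ground is also a safeguard against fraudulent referrals, so weakening it would have a cost of its own.

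**Conclusion.** The point holds in a limited form. The promise in Ethical Considerations and in Results cannot be literally true alongside a payment for each completed screening, because completed screening is data the study team collects. The count of screened peers is disclosed up to the cap of five. The identity of a screened peer is disclosed in some cases, chiefly in small networks or if cards are issued as screenings occur.

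The size under the plan cannot be fixed, because it depends on card timing and itemisation. With a single un-itemised payment, the illustration gives full identification of attendance in 50% to 58% of two-peer networks and 6% to 17% of five-peer networks. This rests on assumed screening probabilities of 0.3 to 0.7 and on independence between peers, and it includes networks where nobody screened.

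The documents do not support a conclusion that the assurance fails for every paid peer, or that HIV status, testing, results, PrEP history or enrollment is disclosed. An effect on linkage counts would be speculation.

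**What to change.** 1. Reword the assurance in Ethical Considerations and in Results, and in the coaches' script. It should say that no health information or screening answers are shared with the ambassador, but that the ambassador is paid per completed screening and may be able to infer that the peer was screened. This is needed under any payment schedule, because small networks remain identifiable.
2. Issue referral compensation as one un-itemised amount when the ambassador's outreach closes, at most six weeks after the first coaching session. Instruct coaches not to confirm which peers were screened.

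The amount, the cap and the link to screening stay as they are, so the protection against coercion is kept. The ambassador-facilitated meeting and the dismissal grounds need no change on this account.

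The cost is an IRB modification of the script and payment schedule, plus a wait of up to six weeks for referral payments, which may slightly reduce ambassadors' motivation.
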